## Abstract

**Background:**

This study is in regard to the comparison of whole brain radiation therapy for synchronous brain metastases with irradiation protecting the hippocampus versus whole brain radiotherapy for sequential brain metastases to boost irradiation in the treatment of brain metastases from small cell lung cancer (SCLC). Therapeutically, they have notably varying dose distributions. Based on theoretical and model studies, it has long been speculated that these modes may result in different prognostic outcomes. We aim to assess the efficacy of tomotherapy in the treatment of SCLC brain metastases while protecting the key functional area, the hippocampus, and minimizing any neurocognitive impairments incurred by radiation.

**Methods:**

This is a randomized, controlled, prospective study including 102 SCLC patients with brain metastases randomized (1:1) to the experimental (whole brain radiation therapy for synchronous brain metastases with irradiation to protect the hippocampus) or control (whole brain radiotherapy for sequential brain metastases to boost irradiation) group. The sample size is calculated through a single-sided test; 102 participants will be required for the main results to have statistical and clinical significance. We aim to provide clinical trial data support for better prognostic treatment options in patients with SCLC and brain metastases. The clinical trial data include both the primary and secondary outcomes; the primary outcome is the intracranial progression-free survival time after the new technology application. The secondary study outcomes include the assessment of neurological function, the quality of life, and the overall survival rate. Follow-up consultations will be conducted every 2 months. After the final patient completes follow-up, the Statistical Product and Service Solutions software will be used for scientific and rigorous data analysis. Version 1.0 of the protocol was implemented on January 1, 2021; the recruitment process for this clinical trial commenced on April 1, 2021, and will end on March 31, 2024.

**Discussion:**

The study will provide high-quality clinical evidence to support the efficacy and safety of whole brain radiation therapy for synchronous brain metastases with dose irradiation protecting the hippocampus versus whole brain radiotherapy for sequential brain metastases with push volume irradiation for the treatment of patients who have lung cancer as well as brain metastases. This has not been previously reported.

**Trial registration:**

This trial is registered with the Chinese Clinical Trial Registry (ChiCTR1900027539; November 17, 2019) (URL: https://www.chictr.org.cn/hvshowproject.aspx?id=20515).

## Background

Approximately 80% of small cell lung cancer (SCLC) patients develop brain metastases during the entire course of the disease [1, 2]. The craniocerebral brain is one of the common metastatic sites for SCLC and is mainly treated by radiation therapy, which can significantly prolong the survival time of patients [3]. Whole brain radiotherapy (WBRT) is a basic radiation therapy specially employed in patients with extensive brain metastases [4–6]; however, it is associated with side effects including neurotoxicity and cognitive dysfunction. Radiation-induced hippocampal damage plays an important role in cognitive dysfunction; thus, avoiding the hippocampus can effectively reduce the cognitive impairment attributed to WBRT [6–9].

Studies have shown that the metastasis rate of SCLC in the hippocampus is approximately 3–5.1% [10–13]. Modern radiotherapy modalities include conventional three-dimensional conformal radiation therapy (3D-CRT) and intensity-modulated radiation therapy (IMRT) [14]. Spiral tomotherapy (TOMO) is another novel method in the field of IMRT technologies that uses a spiral 360° radiation transmission system, similar to that of spiral computed tomography (CT) scanning. Most planning studies have demonstrated that IMRT can fully treat the target volume while retaining healthy organs and tissues, thereby outperforming 3D-CRT [15–17]. Compared with traditional fixed-field IMRT, TOMO possesses the advantage of the use of more independent ray directions, which could result in better dose adaptation to the target. By quickly opening and closing the blades in a collimator rotating around the patient, TOMO can maintain the radiation dose in a tumor area of complex shape, while preventing exposure of normal, healthy organs to radiation [18, 19]. Compared with 3D-CRT, TOMO can reduce the number of tissues irradiated at a dose level equivalent to the tumor dose and redistribute the excess dose to normal tissues, thereby resulting in a total integrated dose that is smaller than that required by 3D-CRT [20, 21].

Currently, TOMO is often used for a variety of diseases [22–24]; however, the clinical value of TOMO in the treatment of SCLC brain metastasis remains controversial. There is a substantial difference regarding the dose distributions of the abovementioned technologies. Based on theoretical and model studies, it has been long speculated that different doses may result in different prognostic outcomes. Therefore, this study sought to use TOMO technology to implement WBRT synchronous irradiation of brain metastases with increased radiation doses, while protecting the key functional areas of the hippocampus.

Our primary hypothesis is that TOMO will increase the clinical intracranial progression-free survival (iPFS) time by approximately 5–8%, owing to the higher accuracy of the treatment plan regarding location and dose of local tumor control. Our secondary hypothesis is that neurological function will be better protected due to the accuracy of this therapy. In the future, we hope to develop intervention methods and improve the corresponding treatment protocols based on the results of this clinical trial. This clinical trial is expected to further improve the efficacy of radiotherapy and improve the quality of life and survival of patients.

## Methods/design

### Study settings

This clinical trial will be conducted at the Liaoning Cancer Hospital Medical Center (a tertiary care center) in China. This is a prospective study enrolling 102 patients. We aim to investigate the safety and efficacy of radiotherapy in patients with brain metastases caused by SCLC using the TOMO treatment device. Using the random number table method, a random number sequence will be generated, and patients will be assigned to the experimental and control groups in a 1:1 ratio. The experimental group will use TOMO, while the control group will use three-dimensional conformal radiotherapy (conventional 3D-CRT)/intensity-modulated radiation therapy tomotherapy (IMRT). This study will not use blinding of trial participants since the treatment procedure clearly distinguishes between the trial and control groups.

The trial sponsors are the Shenyang Major Scientific Research Projects [No. 191124090] and the Cancer Research Program of National Cancer Center [NCC2017A08]. This is version 1.0 of the protocol as of January 1, 2021. Recruitment for this clinical trial began on April 1, 2021 and will end on March 31, 2024.

### Study participants

Liaoning Cancer Hospital is a tertiary specialty hospital in Liaoning Province, China, with a large number of oncology radiotherapy patients each year. The patient’s treating physician explains this clinical trial to patients who meet the enrollment criteria and obtains the patient’s consent to achieve sufficient participant enrollment. A computer will automatically generate the allocation sequence using the random number table method. Team investigators will recruit participants and assign them to the intervention. Assignments will be implemented using sequentially numbered, opaque, and sealed envelopes that are unknown to the investigator who contacts the participant prior to assigning the intervention. Since the trials are all clinical treatments, compliance is good, and the experimental progress can be viewed according to the archive of treatment cases in the computer.

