### Sample size

It will be necessary to evaluate differences between the two groups; thus, the sample sizes of the experimental and control groups were set as n1 and n2, respectively. The two groups should have the same sample sizes; therefore, a single-sided test was used. The sample size calculation formula was:$${n}_1={n}_2=2{\left[\frac{\left({z}_{\alpha }+{z}_{\beta}\right)\sigma }{\delta}\right]}^2$$

where σ is the overall standard deviation (estimated to be 1.84); δ, the difference between the two sets of numerical variables (estimated to be 1); Zα, the standard normal value corresponding to the inspection level α; and Zβ, the standard normal value corresponding to β. If *σ* = 1.8 months, *δ* = 1 month, *α* = 0.05, *β* = 0.20, Zα/2 = Z0.05/2 = 1.96, and Zβ =Z0.20 = 0.842; then, by substituting the above formula, we obtain$${n}_1={n}_2=2{\left[\frac{\left(1.96+0.842\right)\times 1.8}{1}\right]}^2=50.9\approx 51$$

Hence, 51 cases will be included in the control group and 51 cases in the experimental group, with the total sample size being 102 cases.

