### Data analysis

After the last patient completes the follow-up study, the committee will assess the occurrence of the primary and secondary endpoints. Treatments in participant timeline are all routine medical orders, and patients will follow the medical advice. If there is any failure to review on time, a phone call will be reminded. If the patient fails to complete the relevant examination, evaluation or follow-up within the agreed time, or cannot suspend the study, part of the clinical trial of the patient will be suspended. The data of these patients will be marked on the record and not entered in the final curative effect analysis system. The fixed staff is responsible for the input of data, coded into groups 1 and 2 according to their treatment plans, and set a password for the database to protect the privacy of patients’ data. Data quality is controlled by the Data Quality Supervision Committee.

Data will be organized and analyzed using the SPSS 25.0 software, and *P* < 0.05 will be considered significant in all statistical tests. iPFS and OS will be calculated using the Kaplan-Meier method. Assessment of neurological function will be scored using the EDSS assessment scale, and QoL will be scored using the FACT-G. The chi-squared test will be used in combination with propensity matching analysis to minimize differences due to smoking, sex, weight loss, geographic factors, economic status, and education level and to avoid baseline effects to the greatest extent possible. Definition of analysis population relating to protocol non-adherence is that the patients who do not follow. In addition, we use the multiple imputation method to handle missing data.

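### No stratification factor is stated, and the number of brain metastases appears neither in the allocation nor among the factors to be balanced afterwards

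*Protocol article*

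**What the plan says.** Allocation is described in two places. Study settings says a random-number sequence will be generated and that "patients will be assigned to the experimental and control groups in a 1:1 ratio". Study participants adds: "A computer will automatically generate the allocation sequence using the random number table method", implemented through sequentially numbered, opaque, sealed envelopes. Neither section mentions strata, blocks or minimisation, and neither says that the sequence is unrestricted. Sample size plans that "51 cases will be included in the control group and 51 cases in the experimental group".

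Baseline differences are taken up again under Data analysis: "The chi-squared test will be used in combination with propensity matching analysis", the aim being "to minimize differences due to smoking, sex, weight loss, geographic factors, economic status, and education level". Number of metastases is not in that list.

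Three other sections show why lesion number matters here. The inclusion criteria admit patients with up to five brain metastases. The Treatment plan gives both arms a boost aimed at the metastases, simultaneous in one arm and sequential in the other. The primary outcome is iPFS.

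**The concern.** The authors plainly expect baseline differences to matter, since they commit to a method for reducing them. The factors they chose are mostly social and demographic. The one characteristic that defines the target of the boost, and that sits closest to an intracranial endpoint, is left to chance at allocation and is absent from the later balancing. It must be known at the eligibility screen, because entry depends on it, so using it needs no new data.

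At stake is how the iPFS result can be read. If one arm happens to have more patients with a single lesion, an unadjusted comparison mixes that difference with the treatment contrast, and readers of a 102-patient open trial will ask about it.

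**Working it through.** **1. The plan's own figure.** With SD 1.8 months, difference 1 month and z-values 1.96 and 0.842:

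n per arm = 2 × [(1.96 + 0.842) × 1.8 / 1]² = 50.88, rounded up to 51.

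This agrees with the article's 50.9 and 51, a total of 102. (The same section calls the test one-sided and also gives the SD as 1.84. Those are separate matters and do not affect this point.)

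**2. Chance imbalance in lesion number.** Let p be the share of patients in one category, for example a single metastasis. The article gives no distribution, so p is assumed to lie between 0.2 and 0.5. With about 51 per arm, the between-arm difference in proportions has standard error √[2p(1 − p)/51]:

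- p = 0.2: √(0.32/51) = 0.079, so 10 points is 1.26 standard errors, two-tailed probability about 21%.
- p = 0.3: √(0.42/51) = 0.091, 1.10 standard errors, about 27%.
- p = 0.5: √(0.50/51) = 0.099, 1.01 standard errors, about 31%.

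Simulation of 200,000 trials per setting agrees:

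| Assumed share p | Simple: ≥10 points | Simple: ≥15 | Simple: ≥20 | 51/51, no strata: ≥10 | ≥15 | ≥20 |
|---|---|---|---|---|---|---|
| 0.2 | 20.7% | 5.9% | 1.1% | 17.2% | 6.2% | 0.9% |
| 0.3 | 27.2% | 9.9% | 2.8% | 23.4% | 10.5% | 2.3% |
| 0.5 | 30.6% | 13.6% | 4.3% | 27.6% | 13.8% | 3.7% |

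Holding the arms to 51 each does little for lesion balance. Much of the drop in the 10-point column comes from whole numbers: 5/51 is 9.8 points, so reaching 10 points takes 6 patients (11.8 points). At 15 points the two schemes are practically the same.

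**3. With stratified blocks.** Two lesion-number strata and randomly mixed blocks of 4 and 6 (assumed sizes), 4,000 simulated trials at each of p = 0.3 and p = 0.5: the largest between-arm difference in lesion category was 5.2 points, so none reached 10. Arm sizes stayed within 3 of 51 and were exactly 51/51 in about 56% of runs. This applies to a trial allocated that way from the start.

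**4. What an imbalance could do to the estimate.** The article gives no effect of lesion number on iPFS. If the category shifted mean iPFS by 1 to 3 months (assumed), an imbalance of 10 to 15 points would move the arm difference by 0.10 × 1 = 0.10 to 0.15 × 3 = 0.45 month, against a planned difference of 1 month.

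**5. Arm size itself.** Under simple allocation, exactly 51/51 has probability 7.9%, and a split of 46/56 or worse 37%. Power at the plan's inputs is 80.1% at 51/51, 79.7% at 46/56 and 78.6% at 41/61, so unequal arms cost at most 1.5 points over this range.

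**The case against.** Two stronger readings are tempting, and the document supports neither. A reader might infer that a random-number table cannot deliver the planned 51 per arm. The text never says the sequence is unrestricted, such a table can be constrained to equal arms (for example by ranking the numbers), and an article may leave blocking detail to the full protocol. Unequal arms would in any case cost almost no power. A reader might also infer that one arm will be filled by force at the end, making the last envelopes predictable. No section describes this, and concealed envelopes are specified.

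Further objections bear on what remains. Chance imbalance under randomisation is not bias, and the test's error rate already allows for it; this stands. The prognostic weight of lesion number is not quantified in the document, and both the category shares and the cut at one lesion are assumptions; this stands too, and it limits the claim about size. Entry criteria on performance status and lesion site already narrow the population, but they leave one to five lesions open. Blocks can make allocations more guessable in an open, single-centre trial; varying, undisclosed sizes reduce that risk without removing it. An analysis plan that is not shown could include lesion number as a covariate. That is possible, but the article itself lists the factors to be balanced, and lesion number is not among them. Finally, weight loss, which is listed, is partly disease related, so the list is not wholly unconnected with the tumour.

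**Conclusion.** The point holds as a modest design improvement. As described, balance on number of metastases rests on chance, and the stated list of balancing factors does not pick it up. For a category held by 20% to 50% of patients (assumed), the chance of a between-arm difference of 10 points or more is about 21% to 31% under simple allocation and 17% to 28% with the arms held to 51 each. The point therefore does not depend on which scheme was used. A difference of 20 points or more is uncommon, at about 1% to 4%. The consequence is lost precision and a result open to question, not a biased comparison. How far the iPFS estimate could move rests entirely on an assumed prognostic effect.

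**What to change.** Before any outcome comparison, prespecify number of brain metastases (1 versus 2 to 5) as a stratum or covariate in the iPFS comparison for all patients, for example through a stratified log-rank test or a Cox model. This costs nothing in data collection and covers patients already allocated.

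For patients still to be randomised, amend the computer-generated list to stratify by the same factor, using permuted blocks of varying size that are not disclosed to recruiting staff. The costs are a second numbered envelope series at one hospital and a mixed allocation scheme that has to be reported. The gain in balance is limited to patients not yet randomised; the article gives recruitment as April 2021 to March 2024 but not how many remain. If none remain, only the analysis change applies. The planned sample size is unchanged.

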### Eligibility criteria

#### Inclusion criteria

Satisfying the diagnostic criteria for conventional 3D-CRT/IMRT and TOMOAn age between 18 and 70 yearsA KPS score of > 80 points at the baseline visitPresence of SCLC brain metastasis, with ≤ 5 brain metastasesNo brain stem or bulbar metastasisNo important organ failureAgreement to participate and sign an informed consent form

#### Exclusion criteria

Severe damage to important organs such as the heart, liver, kidney, etc.Uncontrolled, severe systemic infection, sepsis, or toxicemiaHemoglobin < 80 g/L or white blood cells < 3.0 × 10^9^/L before treatmentAdvanced cancer with anemia, weight loss, or cachexiaHaving participated in other clinical studies

### Sample size

It will be necessary to evaluate differences between the two groups; thus, the sample sizes of the experimental and control groups were set as n1 and n2, respectively. The two groups should have the same sample sizes; therefore, a single-sided test was used. The sample size calculation formula was:$${n}_1={n}_2=2{\left[\frac{\left({z}_{\alpha }+{z}_{\beta}\right)\sigma }{\delta}\right]}^2$$

where σ is the overall standard deviation (estimated to be 1.84); δ, the difference between the two sets of numerical variables (estimated to be 1); Zα, the standard normal value corresponding to the inspection level α; and Zβ, the standard normal value corresponding to β. If *σ* = 1.8 months, *δ* = 1 month, *α* = 0.05, *β* = 0.20, Zα/2 = Z0.05/2 = 1.96, and Zβ =Z0.20 = 0.842; then, by substituting the above formula, we obtain$${n}_1={n}_2=2{\left[\frac{\left(1.96+0.842\right)\times 1.8}{1}\right]}^2=50.9\approx 51$$

Hence, 51 cases will be included in the control group and 51 cases in the experimental group, with the total sample size being 102 cases.

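### The 51 per arm and 80% power come from a formula for uncensored normal means, with conflicting sidedness and SD, so they are not supported for the time-to-event primary endpoint

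*Protocol article*

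**What the plan says.** The Sample size section gives the formula n per arm = 2[(zα + zβ)σ/δ]² and defines its terms: "σ is the overall standard deviation (estimated to be 1.84); δ, the difference between the two sets of numerical variables (estimated to be 1"). It then substitutes σ = 1.8 months, δ = 1 month, α = 0.05 and β = 0.20, with "Zα/2 = Z0.05/2 = 1.96, and Zβ =Z0.20 = 0.842". The result is 50.9, rounded to 51 per arm and 102 in total.

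On sidedness, the same section says: "The two groups should have the same sample sizes; therefore, a single-sided test was used". The abstract agrees: "The sample size is calculated through a single-sided test". The Data analysis section sets significance at P < 0.05 and does not say whether that is one- or two-sided.

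The Primary study outcome section defines iPFS as months from the start of radiotherapy to first evidence of progression. The follow-up section sets 2 years of follow-up for it, and the Data analysis section says: "iPFS and OS will be calculated using the Kaplan-Meier method".

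The Background states the expected effect in other terms: "Our primary hypothesis is that TOMO will increase the clinical intracranial progression-free survival (iPFS) time by approximately 5–8" per cent. The sample size section gives no control iPFS, hazard ratio or number of events, and does not relate the percentage gain to the 1-month difference.

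**The concern.** The formula holds for a fully observed, roughly normal measurement compared by its mean. A time to progression followed for 2 years will normally be censored in some patients and is usually skewed. Its power depends on the number of events and the hazard ratio, and neither appears. This is not detail deferred to an analysis plan: the calculation is written out in full, and it is for a different kind of endpoint.

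The calculation also disagrees with its own description, on sidedness and on the SD. Equal group sizes are no reason for a one-sided test.

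At stake is the only stated justification for 102 patients. If beta = 0.20 stands unqualified, a non-significant result could be taken as well-powered evidence against a benefit when the design does not establish that. With sidedness unsettled, the threshold for the final test is open too.

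**Working it through.** **1. Reproducing the plan's figure.** Inputs from the Sample size section: σ = 1.8, δ = 1, z = 1.96 and 0.842.
2 × [(1.96 + 0.842) × 1.8 / 1]² = 2 × (5.0436)² = 50.9, so 51 per arm. The figure reproduces.
Power at 51 per arm: Φ(1/(1.8 × √(2/51)) − 1.96) = Φ(2.805 − 1.96) = 80.1%.

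**2. The plan's formula under its own conflicting inputs.**

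| Test | SD | n per arm | Power at 51 per arm |
|---|---|---|---|
| Two-sided (1.96) | 1.8 | 50.9 → 51 | 80.1% |
| Two-sided (1.96) | 1.84 | 53.2 → 54 | 78.4% |
| One-sided (1.645) | 1.8 | 40.1 → 41 | 87.7% |
| One-sided (1.645) | 1.84 | 41.9 → 42 | 86.4% |

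Only the two-sided row with SD 1.8 gives 51. The test as worded is one-sided, and the SD as estimated is 1.84.

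**3. The 5–8% gain against 1 month.** One month is 5% of 20 months (1/0.05) and 8% of 12.5 months (1/0.08). The two agree only if control iPFS lies between 12.5 and 20 months. An SD of 1.8 months would then be 1.8/20 = 9% to 1.8/12.5 = 14% of the mean, a very narrow spread for progression times; for exponential times the SD equals the mean.

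**4. Illustration on the time-to-event scale.** Assumptions, none stated in the protocol: exponential times, log-rank test, two-sided 5%, all 102 patients with an event (D = 102). With q = |ln HR| × √D / 2, power = Φ(q − 1.96) + Φ(−q − 1.96).

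- 5% gain: HR = 1/1.05, q = 0.246, power = 4.3% + 1.4% = 5.7%.
- 8% gain: HR = 1/1.08, q = 0.389, power = 5.8% + 0.9% = 6.7%.
- One-sided 5%: 8.1% and 10.5%.
- With 60 to 90 events, two-sided: 5.4% to 6.5%.

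For a 1-month gain on a control mean of m months, HR = m/(m + 1):

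| Control mean (months) | HR | Power, 102 events |
|---|---|---|
| 1.8 | 0.643 | 61% |
| 2 | 0.667 | 53% |
| 3 | 0.750 | 31% |
| 4 | 0.800 | 20% |
| 6 | 0.857 | 12% |
| 10 | 0.909 | 8% |

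**5. What the trial can detect.** HR at 80% power = exp(−2 × 2.802/√D). With 102 events this is 0.574, or about 74% longer iPFS for exponential times (1/0.574 = 1.74). With an assumed 80 events it is 0.534.

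**The case against.** The strongest reply is that the calculation is arithmetically right on its own terms. Taking the plan's SD of 1.8 and its 1-month difference, the formula returns 80.1%. The design effect is 1 month; the 5–8% is an approximate expectation in the Background, and the two can be reconciled. The SD slip costs less than 2 percentage points of power, and the sidedness slip makes 51 more than a one-sided test would need. All of this stands, and it means that neither slip is serious alone. It does not answer the main point: 80% is the power of a comparison of uncensored means, not of the declared endpoint.

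Three stronger readings are tempting and go too far.

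- A reader might infer that the true power is 6–7%. The protocol gives no control iPFS, hazard ratio, event count, distribution or named test, so true power cannot be derived from it. The figure also moves with the assumptions. With a Weibull shape of 2, an 8% longer time means HR = 1.08⁻² = 0.857 and power of about 12%, and a 1-month gain on a short control mean gives far more.
- A reader might infer that 5–8% and 1 month contradict each other. They do not if control iPFS is 12.5–20 months; they are merely unlinked, and that range sits badly with the SD.
- A reader might infer that the single-sided wording leaves the trial underpowered. It works the other way.

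**Conclusion.** The point holds: the stated beta = 0.20 is not supported for iPFS, because it comes from a method for a different type of outcome, and the inputs need reconciling on sidedness and SD. Within the plan's own formula the effect is modest (41 to 54 per arm, depending on which stated inputs are used). On the time-to-event scale the shortfall could be large, but its size is conditional. In every exponential, two-sided scenario shown, with every patient having an event, power is below 80%: from 61% down to 8% for a 1-month gain, and about 6–7% for a 5–8% gain. These figures illustrate how far the claim depends on unstated assumptions; they do not estimate the trial's actual power.

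**What to change.** Keep 102 patients and restate the basis.

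1. Delete the single-sided wording in the abstract and the Sample size section. State two-sided 5% for both the calculation and the analysis.
2. Replace the means formula, and with it the 1.8/1.84 conflict, by an event-based statement. It should give the assumed control iPFS, the number of events expected after 2-year follow-up and dropout, and the hazard ratio detectable with 80% power (about 0.57 if all 102 patients have events, about 0.53 with an assumed 80).
3. Report power for the 5–8% hypothesis as a range, with its assumptions.
4. Withdraw the unqualified beta = 0.20 claim. If the expected effect is smaller than the detectable one, present iPFS as an estimate with a 95% confidence interval.

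The cost is a rewritten section and a less favourable power statement. Enrolment does not change.
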